## Abstract

**Background:**

Prostate cancer (CaP) disproportionately affects Black men in the United States, leading to significant disparities in incidence, survival, and quality of life (QoL). Treatment-related side effects, including urinary dysfunction, pain, fatigue, and psychological distress, contribute to poor long-term outcomes. There is an urgent need for culturally-tailored, technology-based interventions to support symptom self-management and survivorship care.

**Objective:**

This study aims to develop, refine, and evaluate the Survivorship App for Ethnically Diverse Black Prostate Cancer Survivors (SAFE-CaPS), a tailored mobile health intervention designed to enhance QoL, improve symptom self-management, and provide psychosocial support.

**Methods:**

This 12-month stratified randomized clinical trial will enroll 248 Black survivors with CaP (including native born, African-born, and Caribbean-born men) into the SAFE-CaPS intervention arm and standard care (SC) control group (1:1 allocation). Eligible participants are self-identified Black men (including native born, African-born, and Caribbean-born) aged 40 to 80 years with a confirmed CaP diagnosis within the past 5 years who own or are willing to use a smartphone. SC will consist solely of routine oncology or primary care follow-up, including clinic visits, referrals, and supportive services as needed, with no digital components. The SAFE-CaPS intervention, developed using the Insight platform, includes daily and weekly ecological momentary assessments of pain, urinary and bowel symptoms, sleep, fatigue, sexual function, mood, physical activity, and diet; adaptive educational modules addressing treatment-related side effects and culturally grounded survivorship concerns; automated symptom alerts prompting nurse follow-up and provider notification; and engagement features such as reminders, goal-setting, and literacy-appropriate content. Intervention content incorporates culturally tailored messaging, patient narratives, and feedback from prior qualitative work with ethnically diverse Black CaP. Stratified randomization will ensure balanced representation of ethnic subgroups. Primary outcomes include overall QoL. Secondary outcomes include specific symptom domains, mental health (depression and anxiety), health care engagement, and app acceptability. Assessments will occur at baseline, 3, 6, 9, and 12 months, and linear mixed models with intent-to-treat principles will evaluate intervention effects over time.

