**Results:**

The study was funded in 2024, institutional review board approval was received in mid-2024, and the study began recruitment on August 24, 2025. Overall, 6 participants have been enrolled, with 2 in the SAFE-CaPS intervention and 4 in SC. Recruitment is expected to conclude in July 2027. Data analysis will occur in late 2027, with article preparation and publication planned for mid-2028 and early 2029. We hypothesize that SAFE CaPS participants will experience greater improvements in QoL, reduced symptom burden, and higher engagement in care compared to SC.

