Given the persistent symptom burden, cultural variation in survivorship experiences, and limited engagement with supportive care among ethnically diverse Black men with prostate cancer, there is a need for theoretical frameworks that can both inform clinical targets and guide user engagement with digital resources. The Revised Wilson and Cleary Model (WCM) of health-related quality of life [47,48] provides a clinically grounded pathway linking biological function, symptom experience, functional status, and overall QoL, offering a clear rationale for monitoring and managing treatment-related side effects that disproportionately affect Black survivors with CaP. Complementing this approach, the Unified Theory of Acceptance and Use of Technology (UTAUT) [49,50] addresses factors that influence technology adoption and sustained use, including usability, cultural relevance, trust, social influence, and access to supportive conditions. Together, these frameworks provide a comprehensive foundation for designing interventions that are both clinically meaningful and acceptable to diverse Black survivor populations with CaP.

Therefore, this study aims to develop, culturally tailor, and evaluate the Survivorship App for Ethnically Diverse Black Prostate Cancer Survivors (SAFE-CaPS), a mHealth intervention designed to improve QoL, enhance symptom self-management, and strengthen psychosocial support among native-born, African-born, and Caribbean-born Black survivors with CaP. Specifically, this protocol describes the design and methodology of a stratified randomized clinical trial comparing SAFE-CaPS to standard care (SC). We hypothesize that participants receiving SAFE-CaPS will experience greater improvements in overall QoL, reductions in treatment-related symptom burden, and higher engagement in survivorship care compared with those receiving SC.

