Participants in the control arm will receive SC as directed by their oncology providers, which may include clinic visits, specialist referrals, or support services. No additional educational materials, digital tools, or support will be provided by the study team beyond the scheduled assessments. They will not have access to the Insight app or EMAs. Participants in the control group will complete baseline and follow-up surveys through a secure REDCap (Research Electronic Data Capture; Vanderbilt University) link [59]. QoL assessments will be completed via REDCap at months 3, 6, 9, and 12. The planned flow of participants through screening, enrollment, randomization, intervention, and follow-up assessments is presented in Figure 1.

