#### Daily EMAs

The SAFE-CaPS group will have access to the app-based intervention for 12 weeks. During this time, participants will complete daily assessments of various symptoms, including pain intensity and impact, sleep quality, fatigue levels, weight changes, urinary frequency and difficulty, body aches, bowel control, sexual function, and depression or anxiety. Additional measures will assess physical activity frequency, duration, and dietary intake (fruit and vegetable consumption). Participants will also complete daily EMAs for 1 week following their 6, 9, and 12-month QoL assessments. Each daily evaluation is expected to take approximately 5–10 minutes to complete.

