#### Post Intervention Survey

Twelve months post-randomization, participants assigned to SAFE-CaPS will complete a structured online survey via REDCap to assess intervention engagement, usability, and changes in health behavior, based on the UTAUT framework. The survey will evaluate participants' responses to the 4 key intervention constructs: performance expectancy, effort expectancy, social influence, and facilitating conditions, along with their final behavioral intent.

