#### Secondary Outcomes

App engagement and usability will be evaluated based on frequency and duration of use, symptom-tracking interaction, and engagement with educational content. Technology acceptance and behavioral intent will also be assessed using the UTAUT framework, which evaluates performance expectancy, effort expectancy, social influence, and facilitating conditions. These outcome variables will be analyzed at multiple time points to determine the effectiveness of the SAFE-CaPS intervention in enhancing QoL, improving mental health, and supporting symptom self-management among Black survivors with CaP. Additionally, semistructured interviews and focus groups will be conducted to explore app usability, engagement, and perceived benefits.

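### Daily symptom, affect, app-use and technology-acceptance data exist only in the SAFE-CaPS arm and cannot support a comparison with standard care, and no measure of engagement in care is described for either arm

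*Protocol article*

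**What the plan says.** **Hypotheses.** The Introduction expects, besides better quality of life, "reductions in treatment-related symptom burden, and higher engagement in survivorship care compared with those receiving SC". The Abstract (Results) repeats the comparison: "We hypothesize that SAFE CaPS participants will experience greater improvements in QoL, reduced symptom burden, and higher engagement in care compared to SC".

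**Secondary outcomes, first list.** The Abstract (Methods) states: "Secondary outcomes include specific symptom domains, mental health (depression and anxiety), health care engagement, and app acceptability".

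**Secondary outcomes, second list.** The Secondary Outcomes section under Measures names app engagement and usability, technology acceptance and behavioral intent, and qualitative interviews. It then says: "These outcome variables will be analyzed at multiple time points to determine the effectiveness of the SAFE-CaPS intervention in enhancing QoL", and extends that aim to mental health and symptom self-management.

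**Data sources.** Of the controls, Study Recruitment and Procedure says: "They will not have access to the Insight app or EMAs". Their follow-up is by survey: "QoL assessments will be completed via REDCap at months 3, 6, 9, and 12". The Daily EMAs section describes the daily symptom items for one arm, opening with "The SAFE-CaPS group will have access to the app-based intervention for 12 weeks". The technology-acceptance survey is also one-arm and taken once: "Twelve months post-randomization, participants assigned to SAFE-CaPS will complete a structured online survey via REDCap".

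**The concern.** A secondary outcome can address a hypothesis framed against SC only if both arms supply it. Most of the symptom detail in Table 1, and every engagement variable the article defines, comes from the app. The section that should define the comparative secondary outcomes instead lists variables that controls cannot have, and says they will determine effectiveness.

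If that wording stands, a change in EMA scores within SAFE-CaPS could be presented as benefit. Natural recovery, regression to the mean and selective completion of EMAs would produce the same pattern without any effect of the app. The Results section already expects fewer severe symptom episodes, and app symptom reports and alerts come from one arm only. For engagement in care, the trial could end with a stated hypothesis and no data to test it.

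**Working it through.** The check traces each outcome to its instrument, arm and timing.

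| Outcome | Instrument described | SAFE-CaPS | SC | Timing |
|---|---|---|---|---|
| Nine daily domains (pain, sleep, sexual function, fatigue, weight, urinary, bowel, activity, diet) | Daily EMA | Yes | No | 12 weeks, plus one week after the 6-, 9- and 12-month assessments |
| Affect | Weekly EMA (Positive and Negative Affect Schedule) | Yes | No | Baseline, first 12 weeks, then around quarterly assessments |
| App engagement | Usage data | Yes | Not possible | During app access |
| Technology acceptance | UTAUT survey | Yes | No | Once, month 12 |
| Quality of life, including pain, urinary, bowel and sexual concerns | FACT-P | Yes | Yes | Baseline, 3, 6, 9, 12 months |
| Depression and anxiety | PHQ-4 | Yes | No arm restriction stated | Baseline, 3, 6, 9, 12 months |
| Engagement in health care | None named | – | – | – |

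**Cross-check from the payments (Study Compensation).**
- Both arms: 2 × $50 + 3 × $25 = $175, the stated control maximum.
- SAFE-CaPS EMAs: $2 × 7 days × 15 weeks = $210 daily, and $20 × 15 = $300 weekly.
- $175 + $210 + $300 = $685, the stated SAFE-CaPS maximum without the exit interview.

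The gap between arms, $685 − $175 = $510, equals the EMA payments exactly ($210 + $300). The payment plan therefore agrees that only SAFE-CaPS completes EMAs. One sentence in Study Recruitment and Procedure calls Insight the platform for the study groups, but the control-arm paragraph that follows rules it out for controls.

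**Count.** Ten repeated EMA measures (nine daily domains and affect) have 0 of 124 controls. FACT-P and PHQ-4 are the only repeated outcomes scheduled in a way that can cover both arms.

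**The two lists compared.** The Abstract's list has symptom domains, depression and anxiety, health care engagement and app acceptability. The Secondary Outcomes section keeps acceptability and app engagement. It does not list symptom domains, PHQ-4 or health care engagement as outcomes. Its reference to several time points does not fit the technology-acceptance survey, which is taken once.

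**Effect on the primary outcome.** The stated sample size reproduces. A two-sided two-sample t test (sidedness assumed) with effect size 0.39, α = 0.05 and 80% power needs 104.18, so 105 per group; 105 / 0.85 = 123.5, so 124. It rests on FACT-P at 12 months, collected in both arms, and this point does not touch it.

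**The case against.** The strongest reply is that the Abstract does not say its symptom outcomes are the EMA items. It describes EMAs as part of the intervention, then gives assessments at baseline, 3, 6, 9 and 12 months analysed by mixed models, which is the FACT-P and PHQ-4 schedule. FACT-P covers several symptoms and controls complete it. This stands. A reader might infer that all symptom data come from the app arm, or that two of the three comparative hypotheses have no control data. The documents do not support either reading.

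Second, app engagement and engagement in care are different constructs. A reader might take the care-engagement outcome to be collected in the app arm only. In fact no instrument for it is described in either arm. The Measures introduction mentions health care access in general terms, and Multimedia Appendix 3, which details the measures, is not shown and may name one.

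Third, the Analytic Plan describes no before-and-after EMA analysis presented as a treatment effect. It treats EMA counts, alerts and education views as usage, and its treatment model is for FACT-P by randomized group. This also stands: misreading EMA change as benefit is a risk created by the wording, not a planned analysis.

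Fourth, the effectiveness sentence could be read loosely as covering all outcomes, since it mentions quality of life and mental health. But it follows directly on a list of app-use and acceptance variables and refers to them. The mismatch between the two lists, the lack of a named FACT-P symptom score and the single-occasion survey are on the face of the article and do not depend on the appendix.

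**Conclusion.** The point holds in a limited form.

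- The ten EMA measures, app use and technology acceptance have no control data. They cannot support the symptom-burden comparison or the effectiveness claim in the Secondary Outcomes section.
- Symptom burden is partly testable through FACT-P and PHQ-4, but that section names neither as a comparative outcome. Sleep, activity, diet and affect as separately measured domains cannot be compared with SC as described.
- The hypothesis of higher engagement in care has, as described, no data in either arm.

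This rests on two assumptions: that controls complete PHQ-4 in their quarterly survey, since no arm restriction is stated, and that Multimedia Appendix 3 adds no shared care-engagement measure. If it does, the third item reduces to naming that measure in the article. Randomization, the primary outcome and the sample size are unaffected.

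**What to change.** 1. In the Secondary Outcomes section, name the FACT-P prostate-specific concerns score and PHQ-4 depression and anxiety, at 3 to 12 months, as the between-arm secondary outcomes, analysed with the primary model. Give instrument, arms and time points for each secondary outcome, and make the Abstract match. Because the FACT-P score is part of the primary total, report it as a component of that result and not as independent support.
2. Label EMA, affect, app-use and technology-acceptance data as descriptive within SAFE-CaPS. Remove the effectiveness claim for them, and state that the acceptance survey is taken once, at 12 months.
3. Unless Multimedia Appendix 3 already has such a measure, either add a few care-use items to the quarterly survey in both arms or drop the care-engagement comparison from the hypotheses.

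Items 1 and 2 cost only rewording. Item 3 adds at most a few self-report questions to a survey both arms already complete. It is best done now: 6 of 248 participants (2.4%) are reported as enrolled, and control baseline and early follow-up data on care use cannot be recovered later.

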**Results:**

The study was funded in 2024, institutional review board approval was received in mid-2024, and the study began recruitment on August 24, 2025. Overall, 6 participants have been enrolled, with 2 in the SAFE-CaPS intervention and 4 in SC. Recruitment is expected to conclude in July 2027. Data analysis will occur in late 2027, with article preparation and publication planned for mid-2028 and early 2029. We hypothesize that SAFE CaPS participants will experience greater improvements in QoL, reduced symptom burden, and higher engagement in care compared to SC.

**Conclusions:**

This study will provide critical evidence on the feasibility, acceptability, and preliminary effectiveness of a culturally tailored mobile health intervention designed to enhance survivorship outcomes among Black survivors with CaP, informing future large-scale trials and real-world implementation.

**Trial Registration:**

ClinicalTrials.gov NCT06651359; https://clinicaltrials.gov/study/NCT06651359

**International Registered Report Identifier (IRRID):**

PRR1-10.2196/81503

## Introduction

Prostate cancer (CaP) remains a leading cancer diagnosis among men in the United States, with 313,780 new cases and 35,770 deaths projected in 2025 [1]. Among racial groups, Black men have the highest incidence rates nationwide at 191.5 cases per 100,000 compared to 114.5 per 100,000 among white men, and a higher CaP mortality rate (37.2 vs 18.1 deaths per 100,000, respectively) [2]. Black men have a greater likelihood of more advanced or aggressive disease at diagnosis, and they are frequently diagnosed at later disease stages, which limits treatment options and contributes to higher morbidity and mortality rates [3,4].

Disparities in CaP survival among Black men are influenced by genetic susceptibility, limited access to health care, family history, socioeconomic factors, and delayed detection [5,6]. Despite these disparities, the overall 5-year survival rate for Black men with CaP is high at approximately 97% [2]. However, survival does not equate to optimal posttreatment outcomes, as many Black men experience a disproportionate burden of treatment-related complications, psychosocial distress, and lower quality of life (QoL) [4,7-9]. CaP survivorship presents unique and persistent challenges, particularly for Black men, who often face disproportionate burdens of physical, emotional, and social distress [5,10]. Long-term treatment-related side effects such as sexual dysfunction, bowel and urinary incontinence, and mobility impairments can significantly diminish QoL [11-14]. Additionally, concerns about cancer recurrence, medical mistrust, and limited access to survivorship resources create further barriers to effective coping and reintegration into daily life [15-17]. These issues are often intensified by stigma surrounding sexual dysfunction, cultural beliefs about masculinity, and discomfort discussing intimate symptoms, which can delay help-seeking among Black men [9]. Addressing these multifaceted survivorship needs requires culturally tailored interventions that improve symptom management and psychosocial support. While many survivors with CaP face physical and emotional challenges, Black men often experience lower levels of functioning in these areas compared to White men [18-20]. Studies report slower recovery rates, decreased satisfaction with recovery, and higher levels of regret following prostatectomy among Black men [3,21,22].

The Black population in the United States is increasingly ethnically diverse, encompassing native-born Black men, African-born Black men, and Caribbean-born Black men [23,24]. While these groups share genetic similarities, their cultural beliefs, health care–seeking behaviors, and survivorship experiences vary significantly [25,26]. Across the African diaspora, Black men are at particularly high risk for CaP, but this risk is not uniform: native-born Black men have higher CaP mortality than African-born Black men and Caribbean-born Black men living in the United States, whereas some Caribbean-born Black men populations show an even greater likelihood of aggressive disease [27]. These patterns are likely driven by a combination of biological, environmental, behavioral, dietary, and geographic factors, including differences in risk exposures, screening practices, and access to high-quality care [4,28]. Studies suggest that perceptions of CaP, symptom management strategies, and engagement with health care differ based on cultural background, highlighting the need for culturally tailored research and interventions to address CaP disparities [8,9,29]. These needs also vary by ethnicity, particularly in areas such as communication about sexual health, stigma surrounding symptom disclosure, preferences for family involvement, and expectations of provider support, further reinforcing the need for tailored survivorship strategies [8,9,30]. Despite the high survivorship burden, Black men often report slower recovery rates, lower satisfaction with treatment outcomes, and higher levels of regret following prostatectomy compared to White men [18,20,31-33]. At the same time, many face systemic barriers to posttreatment support, including financial constraints, geographic challenges, and medical mistrust. These barriers may limit participation in traditional in-person survivorship programs, underscoring the need for scalable, culturally responsive approaches that address ethnic variation in survivorship priorities [3,34].

Mobile health (mHealth) interventions have shown great promise for supporting survivors with cancer by providing easy access to information, symptom tracking, and virtual counseling [35-39]. This technology is highly relevant for Black men with CaP, as more than 85% of Black Americans own smartphones [40], allowing them to access health resources remotely and overcome traditional barriers to care [41,42]. mHealth solutions also provide a convenient and scalable way to deliver tailored survivorship support, reducing reliance on in-person visits, which may be infrequent, inaccessible, or underused among Black men [39]. Additionally, these tools can deliver real-time symptom tracking, personalized resources, and interactive peer support, which have been shown to improve health outcomes in other cancer populations [39,43]. However, there are very limited existing mHealth interventions focusing on CaP [39,44], and none that are specifically designed for Black men or integrate culturally responsive features to enhance engagement and accessibility [39,44-46]. Given the high smartphone adoption rate among Black men and the potential for digital health interventions to reduce disparities, there is an urgent need to develop a culturally tailored mHealth solution that enhances QoL and addresses the unique survivorship challenges faced by Black survivors with CaP.

Given the persistent symptom burden, cultural variation in survivorship experiences, and limited engagement with supportive care among ethnically diverse Black men with prostate cancer, there is a need for theoretical frameworks that can both inform clinical targets and guide user engagement with digital resources. The Revised Wilson and Cleary Model (WCM) of health-related quality of life [47,48] provides a clinically grounded pathway linking biological function, symptom experience, functional status, and overall QoL, offering a clear rationale for monitoring and managing treatment-related side effects that disproportionately affect Black survivors with CaP. Complementing this approach, the Unified Theory of Acceptance and Use of Technology (UTAUT) [49,50] addresses factors that influence technology adoption and sustained use, including usability, cultural relevance, trust, social influence, and access to supportive conditions. Together, these frameworks provide a comprehensive foundation for designing interventions that are both clinically meaningful and acceptable to diverse Black survivor populations with CaP.

Therefore, this study aims to develop, culturally tailor, and evaluate the Survivorship App for Ethnically Diverse Black Prostate Cancer Survivors (SAFE-CaPS), a mHealth intervention designed to improve QoL, enhance symptom self-management, and strengthen psychosocial support among native-born, African-born, and Caribbean-born Black survivors with CaP. Specifically, this protocol describes the design and methodology of a stratified randomized clinical trial comparing SAFE-CaPS to standard care (SC). We hypothesize that participants receiving SAFE-CaPS will experience greater improvements in overall QoL, reductions in treatment-related symptom burden, and higher engagement in survivorship care compared with those receiving SC.

